# Implementing international osteoarthritis treatment guidelines in primary health care: study protocol for the SAMBA stepped wedge cluster randomized controlled trial

**DOI:** 10.1186/s13012-015-0353-7

**Published:** 2015-12-02

**Keywords:** Osteoarthritis, Implementation, Primary care, General practice, Self-management

## Abstract

**Background:**

Previous research indicates that people with osteoarthritis (OA) are not receiving the recommended and optimal treatment. Based on international treatment recommendations for hip and knee OA and previous research, the SAMBA model for integrated OA care in Norwegian primary health care has been developed. The model includes physiotherapist (PT) led patient OA education sessions and an exercise programme lasting 8–12 weeks. This study aims to assess the effectiveness, feasibility, and costs of a tailored strategy to implement the SAMBA model.

**Methods/design:**

A cluster randomized controlled trial with stepped wedge design including an effect, process, and cost evaluation will be conducted in six municipalities (clusters) in Norway. The municipalities will be randomized for time of crossover from current usual care to the implementation of the SAMBA model by a tailored strategy. The tailored strategy includes interactive workshops for general practitioners (GPs) and PTs in primary care covering the SAMBA model for integrated OA care, educational material, educational outreach visits, feedback, and reminder material. Outcomes will be measured at the patient, GP, and PT levels using self-report, semi-structured interviews, and register based data. The primary outcome measure is patient-reported quality of care (OsteoArthritis Quality Indicator questionnaire) at 6-month follow-up. Secondary outcomes include referrals to PT, imaging, and referrals to the orthopaedic surgeon as well as participants’ treatment satisfaction, symptoms, physical activity level, body weight, and self-reported and measured lower limb function. The actual exposure to the tailor made implementation strategy and user experiences will be measured in a process evaluation. In the economic evaluation, the difference in costs of usual OA care and the SAMBA model for integrated OA care will be compared with the difference in health outcomes and reported by the incremental cost-effectiveness ratio (ICER).

**Discussion:**

The results from the present study will add to the current knowledge on tailored strategies, which aims to improve the uptake of evidence-based OA care recommendations and improve the quality of OA care in primary health care. The new knowledge can be used in national and international initiatives designed to improve the quality of OA care.

**Trial registration:**

ClinicalTrials.gov NCT02333656

**Electronic supplementary material:**

The online version of this article (doi:10.1186/s13012-015-0353-7) contains supplementary material, which is available to authorized users.

## Background

Osteoarthritis (OA) is a joint disease characterized by pain, disability, and impaired quality of life. The OA prevalence increases with age and is growing due to the aging of the population and the epidemic of obesity [1]. OA is one of the leading causes of pain and disability for the adult population worldwide [2] and is one of the major contributors to years lived with disability [3]. The costs of treatment and work-related losses are a considerable economic burden [4]. Knee and hip joint replacements for treatment of advanced OA represent a common inpatient surgery. Due to the growing obesity epidemic coupled with aging of the population, the demand for these procedures is expected to accelerate and quadruple by 2030 [5].

Internationally, evidence-based recommendations and standards of care have been developed to improve OA management [2, 6–8]. There is currently no known cure for OA, but non-pharmacological modalities like education, exercise, and weight reduction represent core interventions [2]. The recent national recommendation for imaging in musculoskeletal diseases in general practice recommends conventional radiographs and not magnetic resonance imaging (MRI) in decisions on indication for joint arthroplasty [9]. However, Norwegian and international research indicate that an overall increased access to MRI will result in an increased number of MRI referrals [10], probably also in people with OA.

Structured approaches and stepped care strategies for OA management in order to endorse quality of OA care have been developed in other countries. While Porcheret et al. developed a stepped care strategy for older adults in primary care with knee pain or knee OA [11], the Dutch stepped care strategy (Beating osteoARThritis (BART)) provided a framework for health care providers and people with hip or knee OA to discuss the optimal timing of the various treatment options [12–14]. In the UK MOSAICS study, practice nurses have been trained to provide OA consultations and follow-ups and coordinate referrals to the multidisciplinary care [15]. In Australia, initiatives to reduce the surgery waiting list have been implemented, for example the Osteoarthritis Chronic Care Program (OACCP) in New South Wales. In this programme, a new model of care is being tested, in which a musculoskeletal coordinator assesses individuals and links them with relevant health care providers to support timely and effective care [16]. During 2008, a Swedish project called ‘Better management of patients with OsteoArthritis’ (BOA) was initiated to improve OA care and reduce sick leave among people with OA [17]. The aim of BOA is to offer evidence-based OA information and exercise according to treatment recommendations [2, 6–8] and that surgical interventions should only be considered if non-surgical treatment has been tried and failed. In 2013, a similar project was started in Denmark ‘Good Life with Arthritis in Denmark’ (GLA:D) [18]. Although the health care systems and the models of OA care are somewhat different across countries, the recommendations in the various national and international guidelines are very similar. Thus, aspects of these approaches are likely to be applicable also for other countries.

In the new health sector reform, the Norwegian Directorate of Health has placed the main responsibility for OA treatment in primary health care [19]. However, recent Norwegian research has indicated that people with OA are not receiving the recommended and optimal treatment [20, 21]. This was particularly evident for receipt of OA information, guidance on lifestyle changes, self-management, and weight management. Previous research in general practice has revealed that general practitioners (GPs) are reluctant to discuss weight issues with their patients [22]. A British study on OA monitoring among GPs revealed that the GPs favoured monitoring physical function, pain, and analgesia use over body mass index (BMI), self-management plans, and exercise advice [23]. The authors suggested that the provision of suboptimal care did not result from lack of knowledge and that interventions to improve OA care must address barriers to GPs engaging in optimal care provision [23]. A study among Norwegian physiotherapists (PTs) in private practice showed that exercise treatment was frequently provided but also revealed that the PTs also provided several other treatment modalities with moderate to low quality of evidence or with no evidence from systematic reviews [24].

While good communication is an important element of health care quality, the GP consultation has a limited duration. This implies a challenge for the GPs with respect to patient communication and restricts the amount of information and guidance that can be included within a short consultation. Current OA guidelines recommend physical activity and a healthy lifestyle [2, 6–8]. However, behavioural changes are hard to achieve, and long-term follow-up may be needed. To support for behavioural changes and self-management is a challenge within a GP consultation. A recent systematic review showed that organized follow-up on change of health behaviour can lead to increased level of physical activity [25]. Apart from private physiotherapy, there have up until recently been few other kinds of services that people with OA can be referred to. Frisklivssentral (FLS) (Healthy Living Centre) is a relatively new Norwegian primary health care service that aims to guide and support health-related behavioural changes for individuals with increased risk of, or those who already have, a disease or illness [26]. PTs represent the majority of employees at FLS, but people with other professions may also work at FLS [27]. Close to half of the Norwegian municipalities had established FLSs by 2014. Earmarked subsidies are granted and other incentives for further development are present [28].

Based on international recommendations for OA care and previous research, the SAMBA model for integrated care for people with hip and/or knee OA in Norwegian primary health care has been developed (Additional file 1) and will be implemented in this study. The purpose of the model is to improve quality of OA care in primary health care services by implementing evidence-based international recommendations for OA care among GPs and PTs. An implementation of the model should ensure the provision of optimal, high-quality treatment, and that GPs and PTs deliver the same consistent message to people with OA. However, according to previous research, implementing new care models is challenging, and a systematic review highlighted that there are ‘no magic bullets’ for improving quality of health care [29], but identifying barriers and enablers of implementing guidelines can guide the selection of more effective implementation strategies that are tailored to address those determinants [30].

The barriers and facilitators may be different at different levels of health care [31]. Grol & Wensing have suggested to categorize barriers to and incentives for change among health care professionals into awareness, knowledge, attitude, motivation to change, and behavioural routines [31]. For patients, knowledge, skills, attitude, and compliance are examples of barriers to and incentives for change. Further, barriers and facilitators at the social, organizational, economic, and political context may be present as well [31]. According to Sanders et al., one key obstacle for a successful implementation in primary care may be to achieve ‘coherence’ of the desired practice change with the GPs [32]. GPs may not be able to overcome the inertia of previous practice, may not have the motivation to change, or may not recognize the new approach as distinct from usual practice [33, 34]. Among determinants of guideline use among PTs in primary were care lack of time, poor availability, and limited access to evidence the most important barriers, whereas awareness of and positive attitudes towards guidelines and evidence-based practice, considering guidelines to facilitate practice, and knowing how to integrate patient preferences with guidelines were associated with frequent use of guidelines [35]. In a recent publication, it is stated that one of the major barriers to implement effective management in OA care is suboptimal patient adherence with aspects of the management programme [36].

Interventions tailored to prospectively identified barriers are more likely to improve professional practice than no intervention or dissemination of guidelines or educational materials [37]. Previous research has showed that successful guideline implementation strategies should be multifaceted and actively engage clinicians throughout the process [38]. To identify barriers and facilitators for our OA care model, we performed three focus groups with eight GPs, six PTs, and three patient representatives, respectively (Additional file 2). Based on these discussions, we developed an implementation strategy tailored to the barriers and facilitators identified by the focus group participants (Table 1). The protocol has been reported using the SPIRIT recommendations and the CONSORT guidelines for non-pharmacological interventions [39, 40].

**Table 1 Tab1:** Multifaceted implementation activities to facilitate the implementation of the SAMBA model for integrated OA care

Target group	Barrier	Activity	Description
Patients	Awareness, knowledge, preference	Education material	All patients receive an OA booklet from the PT with information about OA, treatment, and self-management.
	Awareness, knowledge, compliance	Reminder material, exercise diary	Together with the electronic questionnaire at 3 months, a check-list of recommended OA care will be provided. The patients are asked to keep an exercise diary to register each session.
	Accessibility, availability	Direct access to FLS and PT in private practice, geographically spread PT locations	The PTs working at FLS or in private practice will be asked to prioritize the SAMBA patients by ensuring a quick initial assessment and enrolment in the OA programme. Availability will be ensured by recruiting PTs working at different geographical locations.
General practitioners	Awareness, knowledge, attitude, motivation to change, and behavioural routines	Workshop (provision of information)	The GPs will receive oral and written information on recommended OA care, the PT treatment programme, imaging modalities in OA, and information about the appropriate time to refer to an orthopaedic surgeon. The workshop will be embedded in existing GP meetings, be interactive, and allow time for discussions. SAMBA will be presented as a useful ‘tool’. The PTs will be invited to the GP workshop and vice versa in order to know more about each others’ role in OA care.
	Awareness, knowledge	Education material	The GPs will receive a summary of international guidelines for OA care.
	Awareness, knowledge, attitude, motivation to change, and behavioural routines	Education outreach visits	All general practice clinics will be visited twice during the intervention period. Each clinic will receive a reminder call quarterly by the project coordinator.
	Awareness	Reminder material	Posters, pens, post-it note pads, and mouse mats will be distributed during the workshop.
	Motivation to change	Opinion leaders/endorsement	Local opinion leaders will be identified and asked to promote the intervention among their colleagues. The GPs’ association will be asked to endorse the SAMBA model.
	Awareness, motivation to change	Feedback, audit	Study newsletters will be distributed 3 times a year. Feedback on recruitment rate will be included.
	Accessibility, attitude, behavioural change	Direct access to FLS and PT in private practice	The PT working at FLS or in private practice will be asked to prioritize the SAMBA patients by ensuring a quick initial assessment and enrolment in the OA programme.
Physiotherapists at FLS and in private practice	Awareness, knowledge, attitude, motivation to change and behavioural routines	Workshop (provision of information)	The PTs will be educated in delivering OA care in accordance with clinical guidelines with a standardized patient education material and exercise programme recommendations for patients with OA symptoms primarily from the hip or knee + how to adapt the standard modes of delivery to the needs of the individual OA patient. The PTs will be invited to the GP workshop and vice versa in order to know more about each others’ role in OA care.
	Awareness, knowledge	Education material	The PTs will receive a summary of international guidelines for non-pharmacological OA care.
	Awareness, knowledge, attitude, motivation to change, and behavioural routines	Education outreach visits	All FLSs and private PT practices will be visited twice during the intervention period. Each clinic will receive a follow-up call quarterly by the project coordinator.
	Awareness	Reminder material	Posters, pens, and post-it note pads will be distributed during the workshop.
	Motivation to change	Feedback, audit	Study newsletters will be distributed 3 times a year.
	Awareness, motivation to change	Endorsement, continuing educational points	The Norwegian Physiotherapist Association will be asked to endorse the ActiveA programme and to provide accreditation of the workshop for continuing educational points.

*Dark cells represent intervention periods, and blank cells represent control periods. The inclusion of patients will start on January 15th 2015 and end on June 15th 2016. The last six month follow-up will be in December 2016 and the last 12-month follow-up will be in June 2017

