### The control phase

During the control phase, the GPs and the PTs receive no activities to promote the use of the SAMBA model for integrated OA care or any other facilitation towards an uptake of the guideline recommendations for OA treatment. Participants with hip and/or knee OA included during the control phase may receive physical therapy as usual, but not the patient education programme, the OA information booklet, exercise diary, or any of the other ‘activities’ in the SAMBA model for integrated OA care prior to 12 months post-baseline.

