### The primary outcome measure

The participants with hip and/or knee OA will self-report the primary outcome measure, as well as most secondary outcome measures, at five time points: baseline (shortly after the GP consultation) and then 3-monthly (Table 3). The primary outcome will be patient-reported quality of OA care as measured by the OsteoArthritis Quality Indicator questionnaire, a 17-item questionnaire that includes quality indicators (QIs) related to OA patient education and information, regular provider assessments, referrals, and pharmacological treatment [20]. The items were developed from a literature review of published QIs, expert panels, and patient interviews. The patient self-report questionnaire covers one A4 page with yes/no and ‘not applicable’/‘don’t remember’ as response options, and a previous application has showed acceptable validity and reliability in an OA cohort [20]. The total QI pass rate for each person will be calculated as the total number of QIs they passed, divided by the total number of QIs for which they were eligible. At inclusion, the primary outcome measure may be used to assess the effect of the intervention of the GP consultation, whereas at follow-up, it may be used to assess the total effect of the new model.

**Table 3 Tab3:** Primary and secondary outcomes

	Measurement scale	Time^a^
Primary outcome measure (patient-reported)		
OsteoArthritis Quality Indicator Questionnaire [20]	0–100 % (pass rate)	0, 3, 6, 9,12
Patient-reported secondary outcome measures		
Pain level in hip/knee past week	NRS 0–10	0, 3, 6, 9,12
Stiffness in the hip/knee past week	NRS 0–10	---“---
Hip/knee function in the past week	NRS 0–10	---“---
Patient global assessment of the OA disease	NRS 0–10	---“---
Patient acceptable symptom state (PASS)	Acceptable/unacceptable	---“---
Function (Knee injury and Osteoarthritis Outcome Score OoL subscale [44]/Hip disability and Osteoarthritis Outcome Score OoL subscale [45] (K/HOOS)	4 items, 5-point scale	---“---
Physical activity (frequency, intensity, duration) [47]	3 items	---“---
Daily hours in sitting position	1 item	---“---
Satisfaction with the care provided (from patient experience questionnaires [48])	1 item, 5-point scale	---“---
Health related quality of life (EQ-5D) [49]	5 items, 5-point scale	---“---
Body weight	kg	---“---
Health care use past 3 months		---“---
Patient Specific Functional Scale [43]	NRS 0–10	Pre- and post exercise programme
Adverse events	1 item	Exercise diary

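### The 3-month check-list of recommended care goes to intervention-phase patients with the questionnaire that asks about recommended care, and could cue their answers

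*Protocol article*

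**What the plan says.** Table 1 in the protocol article is titled "Multifaceted implementation activities to facilitate the implementation of the SAMBA model for integrated OA care". Its patient rows include reminder material and an exercise diary, described in one cell that begins: "Together with the electronic questionnaire at 3 months, a check-list of recommended OA care will be provided".

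The section on the control phase says that participants included in that phase may have usual physical therapy, "but not the patient education programme, the OA information booklet, exercise diary, or any of the other ‘activities’ in the SAMBA model". The exclusion lasts until a year after each participant's baseline.

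The section on the primary outcome measure describes the instrument as "a 17-item questionnaire that includes quality indicators (QIs) related to OA patient education and information, regular provider assessments, referrals, and pharmacological treatment". Patients complete it at 0, 3, 6, 9 and 12 months (Table 3). They can answer yes, no, not applicable or don't remember. On scoring: "The total QI pass rate for each person will be calculated as the total number of QIs they passed", over the number of indicators for which that person was eligible.

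The section on statistical analyses makes 6 months the main time point. It plans multilevel mixed models that account for municipality, patient and repeated measurement.

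**The concern.** The check-list and the outcome instrument cover the same subject, namely which elements of OA care are recommended. One tells the patient what should be received; the other asks what was received. In the intervention phase they arrive together at month 3; in the control phase only the instrument arrives.

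The instrument relies on memory and on the patient's own view of what applies, so a list alongside it could change answers without any change in care. A 3-month difference between the phases would then mix better care with cued reporting, and the data could not separate the two. If the 3-month values also help to estimate the 6-month effect, some of that mixture could reach the primary result.

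**Working it through.** The plan states no figure on this point, so the check is a comparison of sections followed by the scoring rule.

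**1. Does the check-list reach one phase only?** The Table 1 row does not name a phase. Three places settle it.
- The table's title says that its rows are implementation activities.
- The control-phase section excludes control participants from every such activity for 12 months. It names the booklet and the exercise diary, both of which Table 1 assigns to patients.
- The exercise diary shares a row with the check-list, and the section on secondary outcomes says that only participants recruited in the intervention phase keep a diary.

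The check-list is therefore an intervention-phase item. The 12-month exclusion covers the control patients' 3-, 6- and 9-month questionnaires.

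**2. Is the primary instrument in the 3-month questionnaire?** Yes. Table 3 lists it at 0, 3, 6, 9 and 12 months.

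**3. Can a list that arrives with the questionnaire reflect better care?** Not care given before that moment. Its immediate influence on the 3-month answers can only be cued reporting, or credit for the list itself as information received.

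**4. Which way could cueing move the score?** Let a patient have p indicators passed out of e eligible, so the pass rate is p/e. The article does not say how a don't-remember answer enters the denominator, so take both readings.
- If it is left out and becomes yes, the rate is (p+1)/(e+1), which is higher than p/e whenever p < e.
- If it is left out and becomes no, the rate is p/(e+1), which is lower than p/e whenever p > 0.
- If it already counts as eligible but not passed, a change to yes gives (p+1)/e, which is higher. A change to no leaves p/e unchanged.
- An item that moves from not applicable to no also gives p/(e+1), which is lower.

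The direction therefore depends on what the list brings to mind: care that was received or care that was not.

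**5. How could a 3-month shift reach the 6-month result?** Call the shift d. The article does not say how time is modelled, so the route has a range.
- *Group difference estimated separately at each visit, complete data:* essentially none of d reaches month 6. With missing data, d enters through patients who have a 3-month but no 6-month value, because the model uses their earlier answers. The sample-size section plans for 30 % drop-out from 194 per group, or 0.30 × 194 ≈ 58 patients per group. How many of these would have a 3-month value is not stated.
- *One common group difference over the four follow-up visits, complete data and equal weights (assumed):* d contributes d/4.
- *3-month values not used for the 6-month estimate:* nothing enters.

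The value of d is unknown in every case.

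**The case against.** **The main comparison is at 6 months.** This stands. The statistical section names no separate 3-month comparison, and month 3 is one of five assessment times. The direct difference in collection conditions lies at a supporting time point.

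**The check-list is part of the strategy.** This stands in part. Table 1 aims it at awareness, knowledge and compliance, so any real change in care or self-management that it produces after month 3 belongs to the effect. That does not cover its immediate influence on the answers it travels with.

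**Much of the cueing is shared.** This is fair. The questionnaire is itself a 17-item list of recommended care, and both phases complete it from baseline. Only the increment from the check-list differs, and it may be small.

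**The order is not stated.** This also stands. An electronic form could show the list only after the answers are submitted, and the article may have condensed that detail. What it does state is that the two come together, and it describes no separation.

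**A stronger reading.** A reader might infer that one cued yes is worth 100/17 = 5.9 points and that this rivals the 10-point difference used for the sample size. The documents do not support this. The 5.9 points are the weight of one item, not an estimate of bias. A mean shift of that size would need a net gain of one yes per intervention patient on average, and nothing indicates that. The 10-point target also belongs to the primary outcome, whose main comparison is at 6 months, not 3.

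**Conclusion.** The point holds as a limited measurement concern. In the intervention phase only, the 3-month pass rate is collected in the presence of a list of recommended care, and the list could cue answers. The size and direction of any such effect cannot be obtained from the documents, so no bias figure should be attached to it.

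A reader might also infer that the 6-month primary result is biased. The documents do not show that. Exposure is indirect and arises only if 3-month values enter the repeated-measures model. The wording of the statistical section suggests that they do, but the article does not fix it.

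The conclusion rests on two readings: that the table's title and the control-phase section together keep the check-list from control patients, and that arriving together lets patients see the list before they finish answering. If the list appears only after submission, the concern falls away. The change is a cheap improvement, not a condition for the trial's validity.

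**What to change.** Provide the check-list only after the 3-month questionnaire has been returned or its response window has closed, and state this for both electronic and paper responders. If it is already shown only after submission, one sentence saying so is enough. The activity is kept; the cost is a short delay of the reminder and a change in the order of delivery.

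The section on trial status reports data collection from January 2015 and still ongoing in October 2015, so some intervention-phase patients may already have had both together. A mid-trial change would give earlier and later intervention patients different conditions, in line with calendar time, which matters in a stepped wedge. The date of the change should therefore be recorded. For patients already past month 3:
- interpret the 3-month difference with the caveat that reporting conditions differed by phase;
- add a sensitivity analysis of the 6-month effect that excludes 3-month values from the model.

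The sensitivity analysis needs no new data. It gives up some information on patients who answered at month 3 but not at month 6, so it belongs beside the main analysis, not in its place.
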